## Abstract

Socio-emotional impairments are key symptoms of Autism Spectrum Disorders. This work proposes to analyze the neuronal activity related to the discrimination of emotional prosodies in autistic children (aged 9 to 11-year-old) as follows. Firstly, a database for single words uttered in Mexican Spanish by males, females, and children will be created. Then, optimal acoustic features for emotion characterization will be extracted, followed of a cubic kernel function Support Vector Machine (SVM) in order to validate the speech corpus. As a result, human-specific acoustic properties of emotional voice signals will be identified. Secondly, those identified acoustic properties will be modified to synthesize the recorded human emotional voices. Thirdly, both human and synthesized utterances will be used to study the electroencephalographic correlate of affective prosody processing in typically developed and autistic children. Finally, and on the basis of the outcomes, synthesized voice-enhanced environments will be created to develop an intervention based on social-robot and Social Story^TM^ for autistic children to improve affective prosodies discrimination. This protocol has been registered at BioMed Central under the following number: ISRCTN18117434.

## Introduction

### Autism Spectrum Disorders

Diagnostic criteria for Autism Spectrum Disorders (ASD) include impairments in communication and social interactions, as well as poor abilities of emotional reciprocity and emotional states recognition (American Psychiatric Association, 2013). North American prevalence of ASD lies between 8.7/1,000 registered in Mexico between 2011 and 2012 among 8-year-old children and 18.5/1,000 registered in the United States in 2016 (Fombonne et al., 2016; Chiarotti and Venerosi, 2020). Although a wide variability in prevalence estimations due to methodological concerns has been observed, there is no doubt of a general trend to increased diagnostics of autism over the last 20 years (Chiarotti and Venerosi, 2020). The growing autistic population strengthens the necessity to better understand this condition in order to improve therapies efficacy.

Reduced amplitude and shorter latency of the mismatch negativity (MMN) component in autistic children and adults whilst listening to affective prosody stimuli has been identified as an electroencephalographic (EEG) correlate due to abnormal early pre-attentive selection cognitive processes (Lindström et al., 2016; Charpentier et al., 2018). Recent studies lead to a common agreement on the general impairment of the so-called “social brain” neural network in ASD (Sato et al., 2017; Schelinski et al., 2017). Brain areas of this network are responsible for social cognition and overlap with the Default Mode Network (Subbaraju et al., 2018) and the Action Observation Network (Delbruck et al., 2019). Those brain regions interactively work to allow the successful development of social and emotional complex skills such as social imitation, face recognition, understanding of others’ mental states, communication via verbal utterances and non-verbal behaviors, and recognition and expression of emotions. Brain areas of this networks’ interplay generally depicted as impaired in ASD mainly include the inferior frontal gyrus, the medial and dorsomedial prefrontal cortices, the amygdala, temporal areas including the temporoparietal junction, the middle temporal gyrus and the superior temporal gyrus and sulcus, the orbitofrontal cortex, and the posterior cingulate cortex (Sato et al., 2017; Subbaraju et al., 2018; Delbruck et al., 2019; Francis et al., 2019). Interestingly, the superior temporal sulcus contains “non-primary” auditory neurons involved in extracting complex acoustic information after receiving inputs from the primary auditory cortex, mainly the Heschl’s gyrus responsible for low-level acoustic feature extraction (Samson et al., 2011). The superior temporal sulcus has been characterized as the human “voice area,” responsible for voice identity recognition (Schelinski et al., 2017) and is highly involved in emotion prosody processing (Rosenblau et al., 2016). This area showed weaker activity in autistics and less functional connectivity with the amygdala compared to typically developed (TD) individuals while processing emotional prosody (Rosenblau et al., 2016). Thus, autistics may be impaired in extracting complex auditory features that characterize emotional prosody stimuli and fail to allocate social emotional value.

### Psychoacoustic Properties of Auditory Information

Low interest for speech and atypical distressing reactions to some noises (Schauder and Bennetto, 2016) usually comes along with high interest for music and intact low level auditory abilities (e.g., non-vocal pitch discrimination) in ASD (Globerson et al., 2015; Schelinski and von Kriegstein, 2019). Autistic individuals also show typical abilities to recognize emotional and pragmatic intonations in music (Quintin et al., 2011; DePriest et al., 2017). Vocal emotion recognition abilities have been associated with vocal pitch discrimination skills, and lower emotional prosody recognition capacities have been associated with higher autistic severity (Schelinski and von Kriegstein, 2019). Impairments in emotional prosody recognition observed in ASD may be triggered by psychoacoustic properties of auditory stimuli. While intonation discrimination in music and non-vocal auditory stimuli stem from the accurate processing of local information (e.g., frequency fluctuations and harmonic contour), speech is a highly noisy signal and prosody recognition requires the coordination between a coarsier local processing and higher-level ones (e.g., social allocation, complex acoustic patterns processing) (Zatorre and Baum, 2012; DePriest et al., 2017). In essence, the complex property of vocal sounds defined by its naturalness (i.e., speech comes from the human vocal tract) triggers the difficulty for autistics to discriminate emotional prosodies. In fact, the autistic processing style characterized by the highly accurate local information extraction [Enhanced Perceptual Functioning theory (Mottron et al., 2006)], along with the low ability to integrate the information into a global representation [Weak Central Coherence theory (Happé and Frith, 2006)], may be disadvantageous for developing speech processing abilities. Therefore, the present study aims to identify the physical acoustic properties that characterize naturalness (i.e., specific complexity of vocal sounds) in speech in order to modulate psychoacoustic features of voice that could improve the emotional prosody recognition in ASD.

### Emotional Prosody Recognition

Vocal emotion recognition relies at least partly on the perception of the acoustic properties of the stimulus. In fact, similar acoustic indicators (e.g., pitch, intensity) of emotional prosody have been stressed across cultures (Paulmann and Uskul, 2014), highlighting a universal reliance on the physical acoustic characteristics to recognize emotions in voice. Acoustic physical properties generally recognized as differentiators of emotional prosodies are spectral features, intensity/energy, and rate (Kamińska, 2019). In emotion classification studies, the most considered spectral features are the Mel Frequency Spectral Coefficients (MFCC) (Caballero-Morales, 2013), pitch (fundamental frequency), formants, jitter, shimmer, and harmonics-to-noise ratio (Arruti et al., 2014). So far, culture-specific ways of uttering emotions have been revealed (Paulmann and Uskul, 2014). For instance, English-speakers from Singapore tend to allocate more intensity and higher pitch when expressing anger than English-speakers from Kenya (Laukka et al., 2016). Therefore, although emotional prosody recognition relies on universal norms, cross-culture variations make each ethnic group unique in its way of uttering emotions and listeners from one ethnic group skilled at recognizing emotions uttered by speakers of their own culture. The European Union funded the Interface project to create a public database of emotional utterances in French, Castilian Spanish, Slovenian, and English languages (Hozjan et al., 2002; Emotional Speech Synthesis Database, 2012). Particularly, the Castilian Spanish database contains isolated words uttered by adult male and female voices with neutral, angry, sad, joyful, afraid, disgusted, and surprised prosodies (Hozjan et al., 2002). The Interface database was generated for research purposes to analyze and classify emotional speech. Its subjective evaluation (i.e. the emotion recognition by 16 non-professional engineering students listeners) has shown up to 90% accuracy for correct emotions recognition (Hozjan et al., 2002). Up to now, no emotional speech database in Mexican Spanish containing isolated words uttered with anger, sadness, happiness, fear, disgust, and neutral prosodies is publicly available yet (Caballero-Morales, 2013). Therefore, one aim of the present study pursues to generate a database for adult male, female, and childish voices.

### EEG Signature of Emotion Recognition

To record the brain signature of emotions differentiation in voice, soundless methods may be more suitable since the recording process does not interfere with the acoustic stimulus that has to be processed. EEG, and particularly the analysis of Event-Related Potentials (ERPs), has been widely used to study the neuronal activation process of emotions. Furthermore, thanks to its high temporal resolution, ERPs analysis enable the distinction within attentional, sensory, and higher cognitive stages (Fan and Cheng, 2014). Early automatic auditory perception is usually observed between 100 and 250 ms over frontal and central cortices after stimulus onset (MMN). Higher amplitude of this component indicates higher discrimination of acoustic modulations relative to constant auditory background (Charpentier et al., 2018). As an index of acoustic changes early discrimination, the MMN can be used as an indicator of emotional prosody detection (Lindström et al., 2016, 2018; Paris et al., 2018). If automatic changes discrimination was salient enough, involuntary attentional switch to deviant auditory stimuli happens, and is observed 200–350 ms after stimulus onset at fronto-central cortices as a component known as P3a (Lindström et al., 2018; Paris et al., 2018). Early emotional recognition, valence, and arousal identification appear over frontal and central electrodes between 250 and 350 ms after the stimulus onset (Paulmann et al., 2013). The analysis of the amplitude of the P200 component has allowed to distinguish different prosodies such as disgust (high amplitude) and fear (lower amplitude) (Paulmann et al., 2013). This component has shown to reflect the early arousal decoding and may predict the deeper processing of the emotional information observed in the 250–1,000 ms time-window after the stimulus onset (Paulmann, 2016; Steber et al., 2020). The time window between 400 and 1,000 ms has been related to the motivational relevance and extensive processing of the prosodic emotional stimulus. In such window, the observation of the Late Positive Potential (LPP) over centro-parietal recording sites is frequent (Steber et al., 2020). The LPP amplitude is higher in emotional than neutral stimuli, while it is shorter during the emotional down-regulation (Pan et al., 2020).

Event-Related Potentials laterality is still a controversy. Some experimental paradigms have found a right-hemispheric dominance for emotional processing, regardless of the valence (result in accordance with the Right-Hemispheric Hypothesis) (Godfrey and Grimshaw, 2016; Charpentier et al., 2018). The left lateralization for the processing of positive emotions and higher right hemispheric neuronal activity for negative emotions (i.e., the Valence Theory) has also been observed, without denying the possibility of the mutual coexistence of both phenomena (Wyczesany et al., 2018). Although a sparse literature relative to the ERPs analysis underlying the processing of emotional prosody in autistics, a reduced modulation of the neuronal activity by emotions and a lack of hemispheric lateralization has been observed in this population (Lindström et al., 2016, 2018; Charpentier et al., 2018). Remarkably, in a study focused on the processing of emotional words by autistic adults and their corresponding TD controls, the amplitude of the LPP for positive or negative versus neutral words processing did not reach significance for autistic participants. In contrast, higher amplitude were observed for emotional versus neutral stimuli in the TD sample, and group differences were identified for negative versus neutral words (Lartseva et al., 2015).

### Assistive Technology for the Improvement of Emotional Skills in ASD

#### Social Stories^TM^

Various educational approaches have been proposed to improve social and emotional skills in autistics. For example, the so-called Social Story^TM^ intervention drawn-up by Carol Gray showed promising results (Gray, 2010; Kurt and Kutlu, 2019). This practice consists of sharing relevant cues via a rigorous scheme to teach the patient to process correctly specific every-day life situations (Kurt and Kutlu, 2019). Gray (2010) suggested the following advices. First, the content of the stories should be highly personalized to each patient in order to guarantee the comprehension and attention of the patient. Second, third persons and generalizations may help to keep self-esteem safe (Gray, 2010). Third, format, number of sentences, rimes, rhythm must be adapted to the age, preferences, and cognitive skills of the audience (Bee et al., 2018). Fourth, the use of descriptive, perspective, coaching and affirmative sentences would help to convey accurate information (Bee et al., 2018). Finally, interactions with the patient via questions and partial sentences help to maintain the audience focused, which facilitates to monitor the progression of the patient (Gray, 2010). Overall, the intervention must be implemented in a safe, pleasant and friendly environment with the general aim of fostering the learning (Gray, 2010).

Interventions by Social Stories^TM^ present several advantages: thanks to its easy implementation, parents, caregivers, or close friends can help to personalize the stories, and their content can be updated at wish. On the other hand, improvements can be observed in brief implementations and short sessions (5-min sessions over a 1 to 4-week period) (Vandermeer et al., 2015; Kurt and Kutlu, 2019). The Social Story^TM^ approach has been recently adapted to technology-based interventions to enhance the motivation of patients, facility and efficacy of the interventions (Miller et al., 2020).

#### Social Robots

New technologies help to create a safe and predictable social environment, in which the complexity of social cues can be progressively controlled through the intervention time course, thereby generating an optimized atmosphere for autistic patients (Sartorato et al., 2017). In this respect, social robots offer direct, real, and multisensorial social interactions that have been shown to be perceived as “natural” as human ones by autistics (Chaminade et al., 2012). Social robot-based interventions have shown to improve emotion interpretation differentiation, and emotional perspective-taking skills in autistic children. Eventually, those improvements could be generalized to human and daily life social interactions (Scassellati et al., 2018; Marino et al., 2019). As social robots are accepted by autistics and equally perceived as social partners as humans, they give the opportunity to train social skills.

### Current Study

In the light of research advances, the present proposal aims to integrate Social Stories^TM^ and social robots to improve emotional prosody recognition in Mexican autistic children population. This research will be conducted in three stages:

(1)*Mexican Emotional Speech Database (MESD)*: Characterization of emotional prosodies by physical acoustic features in Castilian and Mexican Spanish cultures. Cultural differences will be identified and an emotional speech database for Mexican Spanish will be generated.(2)*Human vs Synthesized Voice*: Defining the naturalness in human speech by physical acoustic properties. Thereafter, previously recorded emotional Mexican Spanish utterances will be edited in order to reduce naturalness in voice. Finally, the neuronal processing of human and newly synthesized emotional utterances will be recorded by EEG and compared between TD and autistic children.(3)*Social Story*^TM^
*and Robot Intervention*: The voices that lead to the better approximation to a typical processing of emotions in stage 2 will be used to implement a Social Story^TM^ and Robot based intervention. The integrative intervention will be tested on a sample of 54 autistic children divided in 1 experimental group of 18 children and 2 control group composed of 18 children each, and 18 TD children, between 9 and 11 years.

## Materials and Methods

### Mexican Emotional Speech Database

First, it is necessary to characterize physical acoustic features of voice recordings uttered with neutral and emotional prosodies for Mexican Spanish language. The main objective of this stage is to create a Mexican Emotional Speech Database (MESD) encompassing adult male, female, and child voices.

#### Sample

Four healthy male, four healthy female adults (between 19 and 35 years), and eight healthy children (between 9 and 11 years) (Stathopoulos et al., 2011) will voluntary participate to speech recordings. Participants will be excluded if they have been diagnosed with any pathology that affects emotional behavior, hearing, or speech, or present sickness traits affecting voice timbre at the time of the study. Participants will be included if they have grown up in Mexico in a cultural Mexican environment (Mexican academic education and family environments) in order to guarantee a Mexican-way of conveying emotions. Participants will be recruited from a public announcement posted on Tecnologico de Monterrey, Campus Monterrey.

#### MESD Speech Corpus Stimuli

Words for speech utterances will be selected from two sources: the single-word corpus from the INTERFACE for Castilian Spanish database (Hozjan et al., 2002; Emotional Speech Synthesis Database, 2012), and the Madrid Affective Database for Spanish (MADS; Hinojosa et al., 2016a, b). For the creation of the MESD, the 24 isolated words that composed the INTERFACE database will be selected and will repeat across emotions. Words from MADS will be selected based on grammatical class and ratings for valence, arousal, qualitative emotion (anger, disgust, fear, happiness, neutral, and sadness), concreteness, familiarity, frequency, and subjective age of acquisition. Specifically, all words will be nouns or adjectives. Their subjective age of acquisition will be strictly under 9-year-old. Valence and arousal ratings of neutral words will be strictly greater than 4 but lower than 6 (on a 9-point scale), whereas emotional words will be selected to have valence and arousal ratings ranging from 1 to 4, or from 6 to 9. A rating superior to 2.5 (on a 5-point scale) for a particular emotion will allow the qualitative categorization of the word into anger, disgust, fear, happiness, or sadness. Words from MADS will be selected in order to ensure that they will be matched for concreteness, familiarity, and frequency ratings. Words selection will be carried out separately for male, female, and mean ratings for all subjects.

Statistical analysis will be used to guarantee that frequency, familiarity, and concreteness are matched between neutral, fear, disgust, happiness, sadness, and anger words. Values obtained for each of these parameters will be analyzed separately with one-way ANOVAs. Normality and homogeneity will be assessed using Shapiro–Wilk and Bartlett tests, respectively. In case of non-parametric distribution of the data, Kruskal–Wallis test will be applied. *Post hoc* tests will be used to statistically assess specific differences (Tukey after ANOVA, Wilcoxon tests with *p*-value adjustment by Holm method after Kruskal–Wallis). In case of significant differences between emotions, outlier values will be identified, and corresponding words will be eliminated until reaching no difference for all of three parameters. We will consider outliers all ratings for frequency, familiarity or concreteness outside the range defined by percentiles 2.5 and 97.5.

Sample size estimation was calculated with G^∗^Power software version 3.1.9.7 (Faul et al., 2007) for Cohen’s d effect size index of 0.8, statistical significance set at *p* < 0.05. Results indicated that 19 words in each emotion would be enough to provide an estimated power of 0.92. The total speech corpus will be composed of 72 words per emotion (24 from INTERFACE and 48 from MADS).

As ratings might vary from Spanish to Mexican cultures (Hinojosa et al., 2016a, b), cross-culture validation will proceed as follows. Two questionnaires will be created using Survey Monkey online Software. On one questionnaire, participants will have to rate familiarity and concreteness; and on the other hand, they will rate valence, arousal, and qualitative emotion (anger, disgust, fear, happiness, neutral, or sadness). The 288 words selected from MADS will be randomly assigned to four lists of 72 words for estimated 20–25 min questionnaires. All lists will be assigned to both questionnaires. Questionnaires will start with participants required to answer demographic questions about their age and gender. Participants will be able to add an e-mail address if they want to enquire about the research. Then, questionnaire purposes and instructions (information about the rating of each variable) will be explained. Instructions will be adapted from the one proposed by Hinojosa et al. (2016a, b) and are detailed in Table 1. Frequency of use will be taken from LEXMEX (Silva-Pereyra et al., 2014).

**TABLE 1 T1:** Instructions for participants to rate words variables.

Variable	Instructions
Familiarity	It refers to how frequently you encounter the word in your day-to-day language, including both written and oral forms. Please rate familiarity in a 9-point scale, 1 being that you very sparsely find the word in your ordinary language, and 9 being that the word is very frequent in your ordinary language
Concreteness	It refers to how concrete versus abstract you think a concept is. For instance, “device” is an abstract concept because it can refer to a wide set of objects, whereas “foot” is a concrete word because it refers to only one specific concept. Please rate concreteness using a 9-point scale: 1 being “very abstract,” 9 being “very concrete”
Valence	It refers to how much you consider a concept negative/aversive versus positive/attractive. Please rate valence using a 9-point scale: 1 being “very negative,” 9 being “very positive”
Arousal	It refers to the level of relaxation versus excitation a concept generates. Please rate arousal using a 9-point scale: 1 being “very low arousal (very relaxing/calming),” 9 being “very high arousal (very stimulating)”
Qualitative emotion	Please rate the word according to how its concept could be associated with the emotions: anger, disgust, fear, happiness, and sadness. Use a 5-point scale, 1 being “nothing at all,” and 5 being “extremely”

Each word will be presented alone in a page, written in 18-point Arial font. The variables to rate with their respective scale will be placed below the word, so that the participant can answer. Scales will be accompanied with labels of extreme values to allow the participant retaining the direction of the polarity of the dimensions. Familiarity will be the first variable to rate, so that participants will not be biased from rating other variables for the same word first. All items will include the optional answer, “I do not know the meaning.” Each question will be able to be answered once. The order of word apparition will be randomized for each participant.

Mean and standard deviation scores for male, female, children, and all together ratings will be calculated for each word. For culture comparisons, one-way ANOVAs will be conducted for each emotion and variable separately on words qualified as referring to a specific emotion in both cultures. Sample size estimation was calculated with G^∗^Power software version 3.1.9.7 (Faul et al., 2007) for Cohen’s d effect size index of 0.8, and statistical significance set at *p* < 0.05. Results indicated that 34 participants in each category (adult male, adult female, and child) would be enough to provide an estimated power of 0.90. For emotion comparisons in Mexican ratings, values obtained for each variable will be analyzed separately with one-way ANOVAs. Normality and homogeneity will be assessed using Shapiro–Wilk and Bartlett tests, respectively. In case of non-parametric distribution of the data, Kruskal–Wallis test will be applied. *Post hoc* tests will be used to statistically assess specific differences (Tukey after ANOVA, Wilcoxon tests with *p*-value adjustment by Holm method after Kruskal–Wallis). In case of cross-cultural differences, outlier values from both Spanish and Mexican ratings will be identified, and corresponding words will be eliminated until reaching no cultural difference, and no emotional difference for Mexican ratings for all of three parameters (familiarity, frequency, and concreteness). We will consider outliers all ratings for frequency, familiarity or concreteness outside the range defined by percentiles 2.5 and 97.5. The final speech corpus from MADS will be composed of 144 words (24 per emotion), so that the final MESD corpus will be composed of 48 words per emotion (24 from INTERFACE and 24 from MADS).

Forty Mexican participants of each category (adult male, adult female, and child) will voluntarily answer the questionnaires. Adults will be aged between 19 and 35 years old, and children between 9 and 11 years old. They will be excluded if they have been diagnosed with any pathology that affects emotional behavior. They will be included if that have grown up in Mexico in a cultural Mexican environment (Mexican academic education and family environments). Participants will be recruited via public posted on Tecnologico de Monterrey, Campus Monterrey.

In all cases, significance will be set at *p* < 0.05. Statistical analysis will be performed with R software (R Foundation for Statistical Computing, Vienna, Austria).

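### The 0.90 power for the Spanish–Mexican word-rating comparison is counted in participants, but the planned test uses words, and words rated in both cultures are treated as independent

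*Protocol article*

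**What the plan says.** All of this is in the Protocol article, section *MESD Speech Corpus Stimuli*.

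- **Data.** Ratings are reduced to word level: "Mean and standard deviation scores for male, female, children, and all together ratings will be calculated for each word".
- **Test.** The Spanish and Mexican ratings are compared as follows: "one-way ANOVAs will be conducted for each emotion and variable separately on words qualified as referring to a specific emotion in both cultures". The normality fallback named in that paragraph is Kruskal–Wallis. No paired or repeated-measures test is named.
- **Power.** The inputs are a Cohen's "d effect size index of 0.8, and statistical significance set at" 0.05, and the result is "Results indicated that 34 participants in each category (adult male, adult female, and child) would be enough to provide an estimated power of 0.90". Forty raters per category are to be recruited.
- **Number of words.** "The total speech corpus will be composed of 72 words per emotion (24 from INTERFACE and 48 from MADS"), and the final MADS set has 24 words per emotion.
- **Questionnaires.** "The 288 words selected from MADS will be randomly assigned to four lists of 72 words", and all lists go to both questionnaires.
- **Acceptance rule.** If cultures differ, outlying values are identified and "corresponding words will be eliminated until reaching no cultural difference". The same sentence requires that Mexican ratings show no difference between emotions.

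Two neighbouring analyses are handled differently. The power for the comparison between emotions is counted in words (19 per emotion, power 0.92). The acoustic culture comparison in *Sound Processing and Analyses* uses a repeated-measures ANOVA.

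**The concern.** There are two mismatches between the power statement, the test and the data.

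1. **Unit.** The test is run on words within an emotion, so its sample size is the number of words. The number of raters affects only how precisely each word's mean is known. A power figure for 34 participants does not carry over to a test on 24 to 48 words.
2. **Pairing.** Only words that qualify in both cultures enter, so the same words stand on both sides. A one-way ANOVA treats the two sets of ratings as separate samples and leaves the spread between words in the error term.

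Both matter because a non-significant result is what lets the word list through. A test that is less sensitive than stated makes it easier to call the list culturally matched. What is at stake is how well shifts in familiarity, concreteness or frequency are screened out of the MADS words.

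**Working it through.** **Inputs from the article:** d = 0.8; alpha 0.05 ("In all cases, significance will be set at *p* < 0.05"), with sidedness not stated and two-sided taken here; 34 per category; power 0.90; 48 MADS words per emotion at the start and 24 at the end. **Assumed:** the correlation, rho, between a word's Spanish and Mexican ratings. The article gives none, so a range is shown.

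**Step 1: reproduce 0.90.** For two independent groups of n, power comes from the noncentral t with 2n − 2 degrees of freedom and noncentrality d × √(n/2). With n = 34 this is 0.8 × √17 = 3.30, and power is 0.9015. A one-way ANOVA with two groups and f = 0.4 gives the same value. Other readings do not match:

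| Reading | Power |
|---|---|
| One-sided, 34 per group | 0.947 |
| Three categories of 34, f = 0.4 | 0.955 |
| 34 in total over two groups | 0.619 |

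Of the readings tried, only two independent groups of 34 observations give 0.90.

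**Step 2: same formula, words as the unit.**

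| Words per culture | Noncentrality at d = 0.8 | Power at 0.8 | Power at 0.5 | Observed shift needed for p < 0.05 |
|---|---|---|---|---|
| 48 | 0.8 × √24 = 3.92 | 0.972 | 0.679 | 0.41 SD |
| 24 | 0.8 × √12 = 2.77 | 0.774 | 0.396 | 0.58 SD |

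**Step 3: allow for the pairing, 24 words.** The unpaired test was simulated on correlated word pairs (40,000 runs per setting). The paired test uses the noncentral t with 23 degrees of freedom and dz = d / √(2(1 − rho)). For example, at d = 0.5 and rho = 0.7, dz = 0.5 / √0.6 = 0.645.

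| True shift | Test | rho 0.5 | rho 0.7 | rho 0.9 |
|---|---|---|---|---|
| None | unpaired | 0.007 | 0.001 | about 0 |
| 0.3 SD | unpaired | 0.10 | 0.06 | 0.01 |
| 0.3 SD | paired | 0.29 | 0.44 | 0.88 |
| 0.5 SD | unpaired | 0.36 | 0.33 | 0.27 |
| 0.5 SD | paired | 0.65 | 0.86 | 0.999 |
| 0.8 SD | unpaired | 0.85 | 0.90 | 0.96 |
| 0.8 SD | paired | 0.96 | 0.998 | 1.00 |

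At rho = 0 the two tests are about equal (0.40 unpaired and 0.38 paired for 0.5 SD), so pairing costs almost nothing if the assumed correlation is wrong.

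**Step 4: would raters as the unit rescue the figure?** The article does not say how many lists a participant answers. If each answers one list on one questionnaire, a word gets 40 / (4 × 2) = 5 raters per category for a given variable. If each answers one list on both questionnaires, it gets 40 / 4 = 10. On either assumption, 34 is not the number of ratings behind a word.

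**The case against.** The strongest reply is that the screen works at the effect the plan was designed for. The 0.77 holds only at 24 words with zero correlation. The pairing complaint needs positive correlation, and then the unpaired test rejects a 0.8 SD shift in about 85–96% of cases even at 24 words. At 48 words the independent-sample figure is 0.97. This stands. The low detection rates belong to a 0.5 SD shift, which is not the design value, and to correlations that the article does not give.

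The article also does not say that the culture test is still being run when 24 words remain. The screen could pass with more words left. Nor must each deletion lower power for a fixed raw shift: the deleted words are outliers, and removing them also narrows the spread between words. Both points stand, so 24 words is the lower end of a range.

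A reader might infer that cultural shifts are easily missed and that every later stage inherits the damage. The documents do not support that reading:

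- Mexican ratings are separately required to show no difference between emotions. The Discussion asks for matching between emotions and does not ask for equality with Spain.
- Half of the final corpus comes from INTERFACE and does not pass through this screen.
- The Stage 3 Social Stories are newly written and recorded.
- In the EEG group comparisons of Stages 2 and 3, all groups hear stimuli from the same corpus. No route is shown from a missed word shift to a biased group contrast.

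None of this makes 34 participants the sample size of a test on words, or makes the two ratings of one word independent.

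**Conclusion.** The point holds in limited form. The arithmetic behind 0.90 is right, but it belongs to two independent groups of 34 observations, and the planned culture test has words as observations. This mismatch is in the text and needs no assumption beyond reading the test as run on word-level ratings, which is how the article describes it. The range of word counts, 24 to 48, gives 0.77 to 0.97 on the plan's own formula.

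The unpaired test is also conservative, with size about 0.7% or less at an assumed correlation of 0.5 or more. It gives away sensitivity to shifts below about 0.6 SD. That loss depends on the assumed correlation and is largest when the list is shortest. It affects the acceptance of the MADS words only and does not reach the intervention outcomes of Stage 3. It should be corrected, but it does not undermine the design.

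**What to change.** - **Test.** For each emotion and variable, compare cultures with a test paired by word: a paired t-test, a Wilcoxon signed-rank test where normality fails, or a mixed model with a word random effect. This matches the repeated-measures approach already chosen for the acoustic culture comparison.
- **Power.** Restate it with words as the unit, for the number of words at which the list is accepted (24 to 48 per emotion), with a stated between-culture correlation. Stop giving 34 participants as the basis for 0.90. If the 40 raters per category are kept, the authors should give their own justification for that number.
- **Limit of the fix.** Pairing does not change the fact that non-significance is read as sameness. Reporting a confidence interval for the mean shift, or judging it against an equivalence margin, would show how large a shift remains possible.

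**Cost.** The test and one power statement change, and no new data are needed. The downside is small: a more sensitive screen may remove more of the 48 candidate words per emotion, of which 24 must remain.
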